### Secondary and Exploratory Outcomes

5.4

Secondary outcomes include diaphragm thickness, forearm muscle thickness, BI scores, and TFI scores. These outcomes will be analyzed using ANCOVA models analogous to the primary analysis, including the same covariates and adjusting post‐intervention values for baseline measurements. Results for secondary outcomes will be interpreted as supportive and exploratory, without adjustment for multiple comparisons. Exploratory analyses will examine associations between changes in muscle thickness (rectus femoris, diaphragm, and forearm) and changes in functional and frailty measures using Pearson or Spearman correlation coefficients, as appropriate, based on data distribution. These exploratory analyses are hypothesis‐generating and intended to inform future studies rather than provide confirmatory evidence.

### Missing Data Handling

5.5

Missing outcome data will be handled using Multiple Imputation by Chained Equations under a Missing at Random assumption, in accordance with SPIRIT and CONSORT recommendations. The imputation model will include group allocation, baseline and post‐intervention values of all primary and secondary outcomes, age, sex, and baseline frailty. Twenty imputed datasets will be generated and pooled using Rubin's rules. Primary ANCOVA analysis will be conducted on the multiply imputed datasets to preserve the intention‐to‐treat principle. As sensitivity analyses, linear mixed‐effects models estimated by maximum likelihood will be fitted to all available repeated measures without ad hoc imputation; additional sensitivity analyses will include complete‐case and per‐protocol analyses. The Last Observation Carried Forward will not be used.

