### Sample Size Calculation

3.3

The primary outcome is rectus femoris muscle thickness (mm), assessed by B‐mode ultrasonography at a standardized mid‐thigh location. A conservative standard deviation (*σ*) of 3.0 mm was assumed based on prior studies in older adults (Berger et al. 2015; Meza‐Valderrama et al. 2022).

Based on previous WB‐EMS trials reporting lower‐limb hypertrophy of approximately 8%–20%, a between‐group difference (Δ) of 2.0 mm (≈13% relative increase) was defined as clinically meaningful (Kemmler et al. 2017). Sample size was calculated for a two‐group ANCOVA model adjusting post‐intervention values for baseline, assuming a baseline–post correlation (*ρ*) of 0.60, two‐sided *α* = 0.05, and 80% power. Under these assumptions, 23 participants per group are required. Allowing for 25% attrition, the target sample size was 62 participants (31 per group).

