### Primary Outcome Analysis

5.3

The primary analysis will follow the intention‐to‐treat principle. Post‐intervention rectus femoris muscle thickness will be analyzed using analysis of covariance (ANCOVA), with group as the fixed factor and baseline rectus femoris thickness as a covariate. Age, sex, and baseline frailty (TFI score) will be included as additional covariates. Adjusted between‐group mean differences will be reported with 95% confidence intervals and two‐sided *p* values. Sensitivity analyses will be conducted using linear mixed‐effects models including time (baseline and post‐intervention), group, and their interaction.

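### Twenty imputations are valid but leave avoidable seed-to-seed noise in the primary p-value; at least 100 would more than halve it at almost no cost

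*Protocol article*

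**What the plan says.** Section 5.5 (Missing Data Handling) plans "Multiple Imputation by Chained Equations under a Missing at Random assumption". It then fixes the number, with pooling by Rubin's rules: "Twenty imputed datasets will be generated". The imputed analysis is the primary one: "Primary ANCOVA analysis will be conducted on the multiply imputed datasets to preserve the intention‐to‐treat principle". The mixed-model, complete-case and per-protocol analyses are sensitivity analyses only.

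Section 5.3 (Primary Outcome Analysis) defines the result that rests on these 20 datasets: "Adjusted between‐group mean differences will be reported with 95% confidence intervals and two‐sided" p-values. The ANCOVA adjusts for baseline thickness, age, sex and baseline TFI.

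Section 3.3 (Sample Size Calculation) reaches 62 participants, 31 per group, after "Allowing for 25% attrition".

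**The concern.** Multiple imputation draws random values, so a different seed gives a slightly different pooled estimate, standard error, degrees of freedom and p-value. The usual reassurance that 20 imputations are about 99% efficient concerns the precision of the estimate over repeated trials. It does not say how closely a second run on the same data would reproduce the p-value. With 62 participants and up to a quarter of outcomes missing, that second quantity is noticeably worse.

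What is at stake is reproducibility near the threshold. Two analysts who both follow section 5.5 exactly, on the same data but with different seeds, could report primary results on opposite sides of 0.05. The protocol itself fixes the number of imputations, so this is not a detail left open for an analysis plan.

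**Working it through.** **Inputs from section 3.3:** difference 2.0 mm, SD 3.0 mm, baseline–post correlation 0.60, two-sided alpha 0.05, power 80%, attrition allowance 25%. **From section 5.5:** m = 20. **Assumed:** the fraction of missing information (FMI), which the protocol does not give.

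**1. The plan's own figure.** Residual SD = 3.0 × √(1 − 0.60²) = 2.4 mm. Per group, n = 2 × (1.960 + 0.842)² × 2.4² / 2.0² = 22.6, rounded up to 23. Then 23 / 0.75 = 30.7, rounded up to 31, or 62 in total. The sample size reproduces exactly.

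**2. Monte Carlo error of the estimate.** As a share of its standard error this is √(FMI/m). Relative efficiency is 1/(1 + FMI/m).

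| FMI | m = 20 | m = 100 | m = 200 | Relative efficiency, m = 20 |
|---|---|---|---|---|
| 0.15 | 8.7% | 3.9% | 2.7% | 99.3% |
| 0.25 | 11.2% | 5.0% | 3.5% | 98.8% |
| 0.35 | 13.2% | 5.9% | 4.2% | 98.3% |

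**3. Effect on the p-value for a fixed dataset.** Trials were simulated with 31 per arm, 8 per arm missing completely at random and residual SD 2.4. They used the protocol's covariates, proper normal-regression imputation of the single incomplete outcome, and Rubin's rules with small-sample degrees of freedom. FMI came out at 0.28–0.29. Each row averages 30 datasets, shifted to have the stated complete-case p-value and re-imputed with 150 seeds for each m.

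| Complete-case p | m | SD of p over seeds | Central 95% of seeds | Seeds with p<0.05 |
|---|---|---|---|---|
| 0.04 | 20 | 0.017 | 0.021–0.086 | 62% |
| 0.04 | 100 | 0.007 | 0.031–0.058 | 83% |
| 0.04 | 200 | 0.005 | 0.034–0.053 | 91% |
| 0.02 | 20 | 0.010 | 0.010–0.050 | 97% |
| 0.01 | 20 | 0.006 | 0.005–0.028 | 99.96% |

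**4. Risk over all trials.** If s is a trial's share of seeds with p<0.05, two independent seeds disagree with probability 2s(1 − s). The averages below are over 800 simulated trials per effect, with 10 seeds each and the finite-sample factor 10/9.

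| True effect | m = 20 | m = 100 | m = 200 |
|---|---|---|---|
| 2.0 mm | 5.4% | 2.2% | 1.6% |
| 1.5 mm | 8.0% | 3.3% | 2.0% |
| 0 | 1.6% | 0.4% | 0.3% |

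A separate simulation of 3,000 trials at 2.0 mm, with three uninformative auxiliary variables in the imputation model, gave 6.7% at m = 20 and 2.7% at m = 100.

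**5. Risk near the threshold.** In those 3,000 trials, 402 (402/3,000 = 13%) had a stable p-value between 0.03 and 0.07. Among them the SD of p over seeds was 0.018 at m = 20 and 0.008 at m = 100, with 30% and 14% of seeds on the other side of 0.05. Smaller sets of 25–30 such datasets, imputed by normal draws and by predictive mean matching, gave SDs of 0.016–0.019 against 0.007–0.008, and 27–31% against 15–18% of seeds. FMI there averaged 0.33 (10th to 90th percentile 0.23–0.43).

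**6. What does not change.** At zero effect the rejection rate in the step 4 simulation was 4.5% at m = 20 and 4.3% at m = 100. At 2.0 mm, power was 72% at m = 20 and 73% at m = 100 and at m = 200.

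**The case against.** Twenty imputations are a valid, prespecified choice. Nothing in section 5.5 is false or contradictory, and the type I error is sound. That stands, and it makes this a refinement and not an error.

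A reader might infer that a borderline result is likely, so that the trial's verdict will turn on the seed. The documents do not support this. A noncentral t calculation with about 41 degrees of freedom puts the chance of a p-value between 0.03 and 0.07 at 11% with 80% power and 14% with 65% power, in line with the simulated 13%. The 30% of seeds on the wrong side applies only within that window. Over all trials at the design effect, the gain from 100 imputations is about 3 to 4 percentage points (5.4 − 2.2 = 3.2; 6.7 − 2.7 = 4.0).

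Nor is 25% a forecast of dropout. Section 3.3 allows for it, and section 4.7 commits to retention efforts and to assessing participants who stop treatment. With less loss, FMI and the noise both shrink.

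Prespecifying a seed would make a re-run identical, and the seed may sit in an analysis plan that is not shown, so its absence here is no fault. A fixed seed makes the answer repeatable, but the answer still depends on one arbitrary draw, and only a larger m reduces that dependence.

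The mixed-model and complete-case analyses involve no random draws and would help to expose an imputation artefact. Section 6 also ties recommendations to the size and consistency of effects. Both points soften the consequence, but the reported primary p-value and interval still come from the 20 datasets.

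**Conclusion.** The point holds as a minor, free improvement. At the full attrition allowance, 20 imputations leave Monte Carlo noise that makes two seeds disagree on p<0.05 in about 5–7% of trials at 2.0 mm, against 2–3% with 100. Near the threshold the noise in p is a little over twice as large at 20 as at 100.

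This rests on an assumed FMI of about 0.3 (roughly 0.2 to 0.4), outcomes missing completely at random in the step 3 and 4 simulations, and the section 3.3 values for SD, correlation and effect. The true FMI also depends on correlations with the secondary outcomes in the imputation model, which the protocol does not give.

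It would be wrong to conclude that the planned analysis is biased or invalid, or that more imputations would buy power. A result with p near 0.01 would stand under practically any seed. More imputations reduce the seed dependence without removing it: a p-value very close to 0.05 can still change sides at 200.

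**What to change.** In section 5.5, replace twenty with at least 100 imputed datasets, preferably 200, generated with a prespecified seed. Report the Monte Carlo error of the primary estimate and of its p-value, so that readers can see whether the result is stable. The seed and the error report may go in the analysis plan; the number must change in the protocol, because that is where it is fixed.

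The cost is trivial computing time for 62 participants: the simulations in steps 3 and 4, by a simplified single-outcome method, ran in about 16 seconds. No further patients, data or assumptions are needed. Section 6.1 sends amendments to the ethics committee before implementation, so there is also a minor administrative step, which can be combined with any other amendment.

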## Discussion

6

Whole‐body electromyostimulation represents a potentially useful adjunct strategy for rehabilitation in individuals with limited tolerance to conventional exercise; however, its physiological and clinical effects in transitional care settings remain incompletely understood. This trial was designed to examine whether WB‐EMS induces measurable changes in muscle thickness during the early post‐hospitalization recovery phase.

Expected physiological adaptations, such as changes in rectus femoris, diaphragm, and forearm muscle thickness, may reflect neuromuscular activation and muscle preservation; nevertheless, the magnitude and consistency of these changes, as well as their translation into functional gains and reduced frailty, remain uncertain. These relationships may be influenced by clinical heterogeneity, baseline frailty severity, comorbidities, and short‐term recovery dynamics typical of transitional care.

From a physiotherapy perspective, ultrasound‐based muscle measures may provide clinically relevant information by capturing early structural adaptations that can precede observable functional improvements. If meaningful associations between muscle thickness changes and functional or frailty outcomes are observed, this may support the selective integration of WB‐EMS as a complementary tool within individualized, multidisciplinary rehabilitation programs for frail, recently hospitalized patients. However, clinical recommendations should be guided by the magnitude of observed effects and their consistency across outcomes.

This study has important limitations. Its single‐center design conducted within a transitional care unit may limit the generalizability of the findings to other clinical contexts and healthcare systems. In addition, the relatively short intervention duration of 6 weeks may not capture longer‐term adaptations in muscle structure, functional recovery, or frailty trajectories. Therefore, inferences regarding sustained or long‐term effects of WB‐EMS should be made with caution.

### Protocol Amendments

6.1

All protocol amendments will be submitted for review and approval by the institutional Research Ethics Committee prior to implementation. Amendments may include changes to study design, eligibility criteria, outcomes, sample size, procedures, or administrative aspects. Following approval, amendments will be documented in the protocol version history, updated on the trial registry (if applicable), and communicated promptly to all members of the research team. Any substantial changes that may affect participant safety or trial integrity will be reported immediately and managed according to institutional and regulatory requirements.

### Ancillary and Post‐Trial Care

6.2

Given the minimal risk nature of the intervention, no additional post‐trial care or extended follow‐up is planned. Should any harm or adverse event related to the study occur, participants will receive appropriate clinical evaluation and treatment according to institutional policies at no cost. After the intervention, participants will return to their routine care provided by the health facility.

### Implications for Physiotherapy Practice

6.3

This study offers evidence‐based insights for physiotherapy researchers investigating novel interventions for frail populations. The WB‐EMS protocol described here may represent a feasible, low‐intensity adjunct to conventional physiotherapy, pending confirmation of clinically meaningful effects to conventional physiotherapy, enhancing muscle structure and functional recovery in hospitalized or recently discharged patients. Findings from this study could help guide the development of standardized and reproducible rehabilitation protocols in geriatric and transitional care settings.

## Ethics Statement

This study was approved by the Research Ethics Committee of the University Hospital, Faculty of Medicine, Federal University of Ceará (UFC), under protocol number 57719422.0.3001.5684, in accordance with ethical standards for research involving human participants. It was also registered in the Brazilian Clinical Trials Registry (ReBEC) under protocol number RBR‐6DQ3QGN.

## Consent

Before the inclusion in this study, all participants will sign an informed consent form.

## Committees and Oversight

A Data Monitoring Committee will not be formed, as the study involves minimal risk intervention and a small number of participants. Monitoring will be carried out by the researchers themselves.

## Data Sharing Plan

Due to the small sample size and the potential risk of participant re‐identification, the sharing of individual participant data (IPD) is not planned. Aggregated results will be included in the final publication, and the statistical code may be provided upon reasonable request to the Principal Investigator. Data will not be deposited in a public repository.

## Dissemination Plan

The study results will be disseminated through publication in a peer‐reviewed journal and presentations at scientific meetings. A lay summary will be made available to participants upon request. The research team holds full responsibility for data interpretation and dissemination.

## Data Availability

The data that support the findings of this study are available on request from the corresponding author. The data are not publicly available due to privacy or ethical restrictions.
